### Study Population

A total sample size of 575 patients, 115 CP recipients and 460 matched controls (1:4 ratio), will be sufficient to detect a clinically important difference of 11.6% between two groups (CP recipients vs matched controls) in 30-day mortality using a two-tailed *z* test of proportions and chi-square test with 80% power and a 5% level of significance. This 11.6% difference represents a 12.4% mortality in the CP recipient group and 24.4% mortality in the matched control patients [23].

The treatment group (CP recipients group) will have 115 patients who have COVID-19 but have not recovered yet as per the inclusion criteria. The control group (comparator group) will have 460 patients who are either not consenting to receive CP or those who will not be able to receive CP due to nonavailability to compare the efficacy of the CP. Control group patients will be subjected to propensity score (PS) matching based on age, gender, diabetes mellitus (DM), hypertension (HTN), and intubation.

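### The mortality rates in the sample-size statement differ by 12.0 points, not the stated 11.6, and the stated 115 + 460 follows from 12.8% with CP rather than 12.4%

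*Protocol article*

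**What the plan says.** The Study Population section of the protocol article gives the only numerical justification for the trial's size. It plans "A total sample size of 575 patients, 115 CP recipients and 460 matched controls (1:4 ratio"), and says that this number "will be sufficient to detect a clinically important difference of 11.6% between two groups" in 30-day mortality, "using a two-tailed *z* test of proportions and chi-square test" "with 80% power and a 5% level of significance". The next sentence breaks the difference into its two rates, citing a published source: "This 11.6% difference represents a 12.4% mortality in the CP recipient group and 24.4% mortality in the matched control patients".

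The abstract repeats the 575 patients, the 1:4 split, the 80% power and the 5% level, but gives no rates. No other section states a mortality assumption that would settle which figure is right.

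**The concern.** The two rates, subtracted, do not give the difference that the same sentence says they represent. At least one of the three printed mortality figures is therefore wrong, and the reader cannot tell which effect the trial was planned to detect.

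This matters because the planning effect, the sample size and the power are the figures on which the trial is approved and against which its result will be read. If the calculation used 12.8% with CP, the printed 12.4% overstates the assumed benefit by 0.4 points. If 12.4% and 24.4% were the true inputs, both the stated difference and the stated power are wrong, and 575 is more than the named test needs.

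**Working it through.** **Inputs, all from Study Population.** CP mortality p1 = 0.124; control mortality p2 = 0.244; stated difference 0.116; 115 CP recipients and 460 controls (1:4); two-sided 5% level; 80% power; z test of proportions or chi-square test, with no continuity correction mentioned.

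**Step 1: the subtraction.** 24.4 − 12.4 = 12.0 points, against 11.6 stated. The gap is 0.4. Figures printed to one decimal can each be off by 0.05, so three of them account for at most 3 × 0.05 = 0.15. Rounding does not explain it.

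**Step 2: the formula.** For the uncorrected z test with pooled variance under the null and four controls per CP recipient, the CP group size is

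n = [1.960 × √(1.25 × p̄(1 − p̄)) + 0.8416 × √(p1(1 − p1) + p2(1 − p2)/4)]² / (p2 − p1)²,

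where p̄ = (p1 + 4·p2)/5.

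**Step 3: reproducing the plan's own 115 + 460.** Keep the stated control rate and the stated difference, so that p1 = 0.244 − 0.116 = 0.128.

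- p̄ = 0.2208
- first term 1.960 × 0.4637 = 0.9089; second term 0.8416 × 0.3972 = 0.3343; sum 1.2432
- n = 1.2432² / 0.116² = 1.5455 / 0.013456 = 114.9, so 115 + 460 = 575

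This is the plan's figure exactly.

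**Step 4: the pair as printed, 12.4% versus 24.4%.**

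- p̄ = 0.2200
- first term 1.960 × 0.4631 = 0.9077; second term 0.8416 × 0.3934 = 0.3311; sum 1.2388
- n = 1.2388² / 0.120² = 1.5346 / 0.0144 = 106.6, so 107 + 428 = 535

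That is 575 − 535 = 40 patients fewer than planned.

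**Step 5: the other one-figure change that gives 11.6 points, 12.4% versus 24.0%.** The same formula gives n = 1.5215 / 0.013456 = 113.1, so 114 + 456 = 570. This is close to the plan but not equal to it.

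**Step 6: power at the planned 115 + 460.** Power is Φ[(p2 − p1 − 1.960 × SE0)/SE1], where SE0 and SE1 are the two square roots above divided by √115. For the printed pair: (0.120 − 1.960 × 0.04319)/0.03668 = 0.964, and Φ(0.964) = 83.2%.

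| Rates (CP vs control) | Difference | Required N | Power at 115 + 460 | Exact chi-square power |
|---|---|---|---|---|
| 12.4% vs 24.4% (as printed) | 12.0 | 107 + 428 = 535 | 83.2% | 83.7% |
| 12.8% vs 24.4% | 11.6 | 115 + 460 = 575 | 80.1% | 80.7% |
| 12.4% vs 24.0% | 11.6 | 114 + 456 = 570 | 80.7% | 81.3% |

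Solving in the other direction, the CP rate that gives 80.0% power at 115 + 460 against 24.4% is 12.81%.

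**Step 7: could another method produce 115 from the printed pair?** The CP group size for 12.4% versus 24.4% is 117 with a continuity correction (117 + 468 = 585; power at 115 + 460 is 79.3%), 116.9 with pooled variance in both terms, 99.8 with the arcsine method, 84.3 with unpooled variance and 83 with a one-sided test. None gives 115, and none alters the 12.0-point difference.

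**The case against.** The strongest reply is that the error is harmless. On every uncorrected reading, 115 + 460 has at least 80% power, so the claim that 575 patients suffice survives whichever figure is misprinted. If the printed rates are right, the trial is slightly larger than it needs to be, not underpowered. Mortality at 30 days is also a secondary endpoint in this protocol. All of this is true. It limits the consequence but does not make the sentence correct, and mortality is the endpoint on which the sample size rests.

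The second reply is that 12.8% is inferred. The protocol never prints it, and the rates come from a reference that is not at hand. Three alternatives come near:

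- 12.4% versus 24.0% falls one CP recipient short of the plan.
- 12.7% versus 24.3% also rounds up to 115 (n = 114.4), although it changes both printed rates.
- With an unmentioned continuity correction, the printed pair needs 117 + 468, close to the plan, which would make 11.6 the misprint.

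This reply stands as a limit on certainty about the cause. The 12.8% reading fits best because it changes one printed figure and matches all the others exactly, but only the sponsor's records can confirm it. By the same logic, the 40-patient gap exists only if the printed pair was the true input. If 12.8% was used, the planned N is right.

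**Conclusion.** The sentence is wrong as written. That the two rates do not give the stated difference is certain: 12.0 points against 11.6. That the planned size does not follow from the printed rates holds for the uncorrected two-sided z test with pooled variance: 535 against 575 patients, and 83.2% power against the stated 80%. The likeliest cause is a CP rate printed as 12.4% where 12.8% was used. This is an inference that takes the 24.4% control rate, the 11.6-point difference and the absence of a continuity correction as correct.

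The practical effect is small. Power at 115 + 460 lies between 80.1% and 83.2% across the three uncorrected readings in the table, and the recruitment target can stay. What has to be settled is which effect the trial was planned on.

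**What to change.** Check both rates against the cited source and the output of the original calculation, then correct the statement so that rates, difference, sample size and power agree:

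- If the CP rate was 12.8%, correct that figure and leave 24.4%, 11.6 points, 115 + 460 and 80% as they are.
- If 12.4% and 24.4% are right, state the difference as 12.0 points and the power at 115 + 460 as 83%. Change the abstract's 80% to match.
- If the control rate was 24.0%, correct it and note that 115 + 460 slightly exceeds the 114 + 456 required, with 80.7% power.

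In each case, say whether a continuity correction was applied. If it was, the power must be restated: 79.3% for the printed pair at 115 + 460. On the uncorrected readings the cost is one corrected sentence (plus the abstract's power in the second case), with no change to patients, endpoints or analysis.

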**Methods:**

Eligible patients with COVID-19 will be recruited for CP infusion according to the inclusion criteria. As COVID-19 has proven to be a moving target as far as its management is concerned, we will use current definitions according to the Ministry of Health (MOH) guidelines for diagnosis, treatment, and recovery. All CP recipients will receive supportive management including all available recommended therapies according to the available MOH guidelines. Eligible CP donors will be patients with COVID-19 who have fully recovered from their disease according to MOH recovery criteria as detailed in the inclusion criteria. CP donors have to qualify as blood donors according to MOH regulations except for the history of COVID-19 in the recent past. We will also test the CP donors for the presence of SARS-CoV-2 antibodies by a rapid test, and aliquots will be archived for future antibody titration. Due to the perceived benefit of CP, randomization was not considered. However, we will compare the outcome of the cohort treated with CP with those who did not receive CP due to a lack of consent or lack of availability. In this national collaborative study, there is a likelihood of not finding exactly matched control group patients. Hence, we plan to perform a propensity score matching of the CP recipients with the comparator group patients for the major characteristics. We plan to collect demographic, clinical, and laboratory characteristics of both groups and compare the outcomes. A total sample size of 575 patients, 115 CP recipients and 460 matched controls (1:4 ratio), will be sufficient to detect a clinically important hospital stay and 30-day mortality difference between the two groups with 80% power and a 5% level of significance.

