### Inclusion Criteria

The inclusion criteria for recipients is as follows:

18 years or olderPatients with COVID-19 confirmed by positive rRT-PCR test for SARS-CoV-2 “using one of the SFDA approved kits used in the Kingdom of Saudi Arabia” as per current MOH guidelinesMust have required intensive care unit (ICU), severe, or immediately life-threatening care:Patient requiring ICU care or admissionSevere disease is defined as dyspnea, respiratory frequency≥30/min, blood oxygen saturation≤93%, the partial pressure of arterial oxygen to fraction of inspired oxygen ratio<300, or lung infiltrates>50% within 24-48 hours.Life-threatening disease is defined as respiratory failure, septic shock, or multiple organ dysfunction or failure.

The inclusion criteria for the donors was as follows:

18 years or olderPrior confirmed COVID-19 diagnosis as per current MOH guidelinesComplete clinical recovery from COVID-19 before donation (at least 14 days from the last SARS-CoV-2 negative polymerase chain reaction or 28 days from the initial symptoms) [15-18]All MOH criteria for blood donation will be followed.All transfusion transmissible infections markers on the donor’s blood are negative as per current MOH routine blood donor screening regulations.Positive rapid serology test for antibodies (IgG) against SARS-CoV-2 indicating immunity against COVID 19

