### Exclusion Criteria

The exclusion criteria for recipients was a negative or nonconclusive COVID-19 rRT-PCR test for SARS-CoV-2, mild symptoms, and hospitalization not requiring ICU care or admission. The exclusion criteria for donors was being unfit for blood donation or a multiparous or pregnant female.

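### No stated rule requires controls to meet the recipients' severity criteria, and intubation is the only severity variable in the match, so less ill controls can dilute the comparison

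*Protocol article*

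**What the plan says.** The Inclusion Criteria section has one list that opens "The inclusion criteria for recipients is as follows" and a second list for donors. The recipient list requires ICU-level, severe or immediately life-threatening disease. The Exclusion Criteria section is again written for recipients and donors: "The exclusion criteria for recipients was a negative or nonconclusive COVID-19 rRT-PCR test for SARS-CoV-2, mild symptoms, and hospitalization not requiring ICU care or admission". Neither section mentions controls.

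The Study Population section describes the treated group as "115 patients who have COVID-19 but have not recovered yet as per the inclusion criteria". The next sentence turns to the comparators: "The control group (comparator group) will have 460 patients who are either not consenting to receive CP or those who will not be able". The second reason it gives is that no plasma is available, and it makes no reference to the inclusion criteria. The abstract defines them in the same way, as "those who did not receive CP due to a lack of consent or lack of availability".

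Controls then undergo "propensity score (PS) matching based on age, gender, diabetes mellitus (DM), hypertension (HTN), and intubation". The Statistical Analysis section repeats these five variables, calls for exact matching on them, and adds regression models whose adjustment factors are not named.

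**The concern.** The comparison is not randomised, so it is only as good as the likeness of the two groups at the start. Recipients have passed a severity threshold. Controls, as written, need only have gone without plasma for one of two reasons. Matching on intubation separates the ventilated from the rest, but it does not separate a non-intubated ICU patient from a non-intubated ward patient of the same age, sex, diabetes and hypertension status.

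The primary efficacy endpoint is ICU length of stay. A control who never needed intensive care has a stay of zero, or none that can be defined, whatever plasma does. Such patients also die less often, so the 24.4% control mortality used for planning would not describe the pool enrolled.

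**Working it through.** **1. The plan's own figure.** For 1:4 allocation (k = 4), two-sided 5% and 80% power, with pooled variance under the null:

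n1 = [1.960·√((1 + 1/k)·p̄(1 − p̄)) + 0.842·√(p1(1 − p1) + p2(1 − p2)/k)]² / (p2 − p1)², where p̄ = (p1 + k·p2)/(1 + k).

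- With the stated difference of 11.6 points below 24.4%, p1 = 12.8% and p̄ = 0.2208. Then n1 = (0.909 + 0.334)²/0.116² = 114.9, so 115 + 460 = 575. The plan's figure is reproduced, with power 80.1%.
- The printed rates, 12.4% and 24.4%, differ by 12.0 points and give 107 + 428, or 83.2% power at 115:460. This discrepancy does not affect the present point. I use 12.8% below because it reproduces the plan.

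**2. What less ill controls do to mortality.** Intubated controls cannot be mild ward patients, so only the non-intubated stratum can be affected. Let s be the share of patients not intubated, m the 30-day mortality of non-intubated controls who meet the severity criteria, and f the fraction of non-intubated controls who do not meet them. Give the latter an assumed mortality of 3%, borrowed from the approximate overall fatality in the Background section. Then

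control mortality = 24.4% − s·f·(m − 3%).

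The article gives none of s, m or f; all are assumptions. With s = 70% and m = 15% (which implies 46.3% mortality in the intubated):

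| f | Control mortality | Power if recipients are at 12.8% | Chance of significant apparent harm if plasma has no effect (recipients at 24.4%) |
|---|---|---|---|
| 0 | 24.4% | 80% | at most 2.5% by design |
| 20% | 22.7% | 67% | 6% |
| 50% | 20.2% | 44% | 18% |
| 100% | 16.0% | 12% | 56% |

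The f = 50% row, for example: 24.4 − 0.7 × 0.5 × 12 = 20.2%.

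**3. Range.** Over s = 50% or 70% and m = 10%, 15% or 20%:
- f = 20% gives power of 61% to 75%, and 4% to 8% chance of apparent harm under no effect.
- f = 50% gives power of 28% to 67%, and 6% to 31% chance of apparent harm.

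The 3% is probably low for hospitalised patients. With 10% instead, at s = 70%, m = 15% and f = 50%, control mortality is 24.4 − 0.7 × 0.5 × 5 = 22.65% and power is 67%.

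**4. Can the sign turn?** Reversing a true 11.6-point benefit needs s·f·(m − 3%) above 11.6 points. At s = 70% and m = 15% the most it can be is 0.7 × 12 = 8.4 points, so it cannot happen. At s = 70% and m = 20% it needs f above 11.6/11.9 = 97%. At s = 90% and m = 20% it needs f above 11.6/15.3 = 76%.

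**5. ICU stay.** If a fraction g of controls were never in intensive care and are counted as zero, the mean control stay is (1 − g) times the mean among the remaining controls. With g = 10% it is 10% shorter before any effect of plasma is considered.

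**The case against.** The strongest reply is that the two permitted reasons already imply a plasma candidate. The section on collecting plasma reserves it for eligible patients, and the section on transfusion links consent to eligible patients with severe disease. A mild ward patient goes untreated because he or she is ineligible, which is not one of the listed reasons. The article's conclusions speak of severe COVID-19, and an ICU-stay endpoint makes sense only for ICU-level patients. This is also a condensed article, with control data forms said to exist.

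Much of this stands. A reader might infer that controls are defined solely by not having received plasma. They are not, and the refusal route in particular suggests someone to whom plasma was offered. But the suggestion is never made a requirement, and the nonavailability route does not need anyone to have assessed eligibility. The opening of the Methods also widens the population to patients at high risk of severe disease. Nor is this only condensation: the article prints the recipient and donor criteria in detail and gives both the control definition and the matching set twice.

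A reader might also infer that the comparison could be reversed. For a benefit of the planned size the documents do not support that. Once intubation matching is allowed for, reversal needs nearly all non-intubated controls to be below the threshold, or a large majority under the most extreme assumptions tried. A simple mixture over all controls would overstate the effect because it ignores that match.

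The unnamed regression adjustment might recover some of the difference. It cannot be relied on while severity is not named in it, and it cannot supply an ICU stay for patients who had none.

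**Conclusion.** The point holds as a gap in the design that should be closed. Nothing in the article obliges controls to have reached the severity required of recipients, and the stated matching set cannot ensure it. The direction of the bias is clear: shorter ICU stay and lower mortality among controls, hence dilution of a true benefit, or apparent harm where the true effect is small or absent.

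The size cannot be established from the documents. The power figures above illustrate what is at stake and rest on assumed shares and assumed mortality by stratum. If sites in fact took only patients who met the recipient criteria, the planned 80% power is unaffected by this point. Confidence is medium, because that may well be what was intended.

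**What to change.** 1. Reconcile the two recipient lists first. The Inclusion Criteria section accepts severe disease as qualifying alongside ICU care, while the Exclusion Criteria section removes inpatients who do not need intensive care. Controls cannot be held to a rule that is unclear for recipients; which version applies is for the investigators to settle.
2. In the Study Population section, state that controls must meet the same age, rRT-PCR and severity criteria as recipients, and differ only in not receiving plasma. Record the date on which these were first met as the index date, in both groups, and draw the matching pool only from these patients.
3. Add baseline severity at that date to the matching or adjustment set: ICU status, oxygenation, and SOFA or APACHE. The Response Assessment section already lists oxygenation and both scores; check that the control form captures them.

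The cost is a protocol clarification, an eligibility check with a date on the control form, and a fuller matching model. The eligible pool will be smaller, so four controls may not be found for every recipient. The achieved ratio should be reported and power restated for it.

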### Response Assessment

The response assessment includes daily clinical assessment by a physician; vital signs including temperature, blood pressure, respiratory rate, and heart rate; oxygen saturation; oxygen requirement; ventilator requirement and the modes employed; inotrope medications requirement; CBCs, liver function tests, urea, creatinine, and electrolytes daily; Apache score; Sequential Organ Failure Assessment score; fluid balance; x-ray or CT changes, repeated every 3-5 days; organs functions assessment; plasma doses and frequency requirement; transfusion-related side effects including TRALI, TACO, etc; and the SARS-CoV-2 RNA will be tested on recovery (or deterioration to determine alternative etiology).

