### Statistical Analysis

Descriptive and inferential statistics will be used to characterize the study sample and test the hypotheses. Descriptive results for all quantitative variables such as age will be presented as mean (SD; for normally distributed data) or median with interquartile range (for data not normally distributed), while numbers (percentage) will be reported for all qualitative variables such as gender.

To assess the independent effect of CP transfusion safety and survival, we will conduct a PS-matching (based on age, gender, DM, HTN, and intubation) analysis. Among the predictors, exact matching will be enforced to achieve the balance for all predictors between the plasma and control groups.

The bivariate analysis will be performed using independent sample *t* test, Mann-Whitney *U* test, Pearson chi-square test, or Fisher exact test whenever appropriate to compare the demographic characteristics (eg, age, gender, nationality) and clinical characteristics (improvement in oxygenation, laboratory parameters, radiological findings, complications, and length of hospital stay) between those who will receive the CP and those who will not receive this therapy.

The multiple binary logistic regression model will be used to assess the effect of CP transfusion on 30-day mortality after adjusting for potential confounding factors compared to matched controls patients. The adjusted odds ratio and 95% confidence interval for the adjusted odds ratio will be reported. The Hosmer-Lemeshow goodness-of-fit statistics will be used to determine whether the model adequately describes the data.

The time-to-event analysis will be measured from the date of diagnosis. The overall survival at 30 days and 3 months will be evaluated using the Kaplan-Meier estimator and compared between the two groups (plasma recipients vs matched control patients) using the log-rank test. A Cox proportional hazard model will also be used to estimate the hazard ratio for in-hospital 30-day mortality for the plasma group compared with matched control group patients after adjusting for potential confounding factors. In addition, interactions between CP administration and all the predictors will be tested to see if the plasma effects will be the same in subgroups. A *P*<.05 (two-tailed) will be considered statistically significant. All statistical analyses will be performed using SPSS version 24 (IBM Corp).

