## Discussion

The study of the Saudi population at risk of severe COVID-19 has some distinct features, as Saudi Arabia was recently challenged by related coronaviruses including MERS-CoV that might lead to distinct immunological responses to SARS-CoV-2. The intention overriding the scientific merit of a randomized controlled trial during this pandemic is an attempt to add CP in the armamentarium against COVID-19, as this readily available agent has historically shown benefit in the treatment of related coronaviruses. There are multiple theoretical and scientific reasons to support our thinking that CP may turn out to be an effective treatment. However, the bottom line is that we do not have enough data to be certain. CP trials that have been published so far have limitations and conflicting data. Our group and others are working hard during this time to establish evidence that could support the therapeutic use of CP for patients with COVID-19.

Limitations of our study include, first, the design of the study, as we could not find it feasible to make the study a randomized controlled trial with our patient population due to the strong perceived benefit of CP in the minds of the patients and treating physicians in this situation. Second, our collaborating centers are of various levels from secondary to tertiary care hospitals with limitation of experience uniformity in conducting such a collaborative study. However, we intend to be a mutually supportive group and keep our study elements uniform. In addition, currently, anti–SARS-CoV-2 antibodies titration facilities are not available countrywide in Saudi Arabia. However, we plan to save aliquots of collected convalescent plasmas to test antibody titers whenever such facilities will be available. Last, we could not include the investigation of some biomarkers like interleukin-6 during treatment in our protocol, due to nonavailability in some centers. Nonetheless, treatment with CP seems promising to treat patients with COVID-19, and a national clinical trial to explore the efficacy and safety of CP is justified.

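### The propensity score is fixed at five variables and leaves out recorded baseline severity beyond intubation, illness duration and prior co-treatment, as well as centre and calendar time; no adjusted analysis is described for ICU stay

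*Protocol article*

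**What the plan says.** Study Population fixes the matching variables: "Control group patients will be subjected to propensity score (PS) matching based on age, gender, diabetes mellitus (DM), hypertension (HTN), and intubation". Statistical Analysis gives the same five: "we will conduct a PS-matching (based on age, gender, DM, HTN, and intubation) analysis". It then adds that "exact matching will be enforced to achieve the balance for all predictors between the plasma and control groups". Neither list is introduced as a set of examples, and neither gives a time point for intubation.

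Controls are "patients who are either not consenting to receive CP or those who will not be able to receive CP due to nonavailability" (Study Population). Eligible severity runs from dyspnea or low saturation up to the top category: "Life-threatening disease is defined as respiratory failure, septic shock, or multiple organ dysfunction or failure" (Inclusion Criteria).

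Other prognostic information is collected. Data Collection lists illness duration and medication, including steroids, tocilizumab and antivirals. Response Assessment lists "Apache score; Sequential Organ Failure Assessment score", oxygen requirement and inotropes. The Discussion says that "our collaborating centers are of various levels from secondary to tertiary care hospitals", and the Abstract describes a changing background: "As COVID-19 has proven to be a moving target as far as its management is concerned".

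Statistical Analysis also plans logistic and Cox models for 30-day mortality, adjusted for confounders that it does not name. ICU length of stay is a primary endpoint (Study Endpoint and Outcome Measures), but no adjusted model is described for it.

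**The concern.** Without randomisation, the comparison is only as good as the set of variables on which the groups are made alike. Whether a patient received CP depended on consent and supply. Supply may vary with hospital and date, and consent may vary with how ill the patient was. Each of these can also be related to death and ICU stay. Two non-intubated patients of the same age, sex, diabetes and hypertension status can match perfectly although one has a low saturation and the other septic shock.

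The untimed intubation variable adds a second difficulty. Days on mechanical ventilation is a secondary endpoint. If intubation after infusion counts for the match, the groups are matched on part of the outcome.

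The final estimate is not all that is at stake. Under Time of the Study, a larger sample and a longer trial depend on the interim showing benefit. The interim (40 recipients, 40 matched controls) is to be analysed in a similar way.

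**Working it through.** **1. The plan's own figure.** Inputs from Study Population: two-sided 5%, 80% power, 1:4 ratio, control mortality 24.4%, difference 11.6 points, hence 12.8% with CP. The pooled formula is

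n = [1.96·√(1.25·p̄(1−p̄)) + 0.8416·√(p1(1−p1) + p2(1−p2)/4)]² / (p1−p2)²

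with p̄ = (0.128 + 4×0.244)/5 = 0.2208. This gives (0.909 + 0.334)²/0.116² = 114.9, so 115 + 460 = 575, as stated. The printed rates, 12.4% and 24.4%, differ by 12.0 points and would give 107 + 428 = 535 without continuity correction. That mismatch is a side observation. The yardstick used below is 11.6 points.

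**2. Score against recorded data.**
- In the score: age, gender, DM, HTN, intubation.
- Listed as collected but not in the score: APACHE, SOFA, oxygen and inotrope needs, days of illness, medication regimen.
- Not listed as data items but implied: centre (multicentre trial) and calendar date (survival time runs from the date of diagnosis).

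**3. Which analyses have further adjustment.**
- 30-day mortality, logistic and Cox: yes, covariates unnamed.
- Bivariate tests, Kaplan-Meier and log-rank: none beyond the match.
- ICU length of stay: no adjusted model described.

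**4. Illustrative size (assumptions, not document figures).** Suppose CP has no effect and control mortality is 24.4%. An unmatched binary severity marker multiplies mortality by RR and is present in a share pC of controls and pT of recipients after matching. Then

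B = [1 + (RR−1)pT] / [1 + (RR−1)pC], and the spurious difference is 24.4 × (1 − B) points.

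Controls sicker (looks like benefit):
- 60% vs 50%: RR 2, B = 1.5/1.6 = 0.938, 1.5 points; RR 3, B = 2.0/2.2 = 0.909, 2.2 points.
- 60% vs 40%: RR 2, B = 1.4/1.6 = 0.875, 3.1 points; RR 3, B = 1.8/2.2 = 0.818, 4.4 points.
- 70% vs 30%: RR 2, B = 1.3/1.7 = 0.765, 5.7 points; RR 3, B = 1.6/2.4 = 0.667, 8.1 points.

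With 115 and 460 patients, the unadjusted two-proportion test would then falsely favour CP with probability of about 5–7%, 10–16% and 24–46% respectively, against a nominal 2.5%.

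Recipients sicker (hides benefit or looks like harm), controls still at 24.4%:
- 50% vs 60%: B = 1.6/1.5 = 1.067 and 2.2/2.0 = 1.10, so 1.6 and 2.4 points.
- 40% vs 60%: B = 1.6/1.4 = 1.143 and 2.2/1.8 = 1.222, so 3.5 and 5.4 points.
- 30% vs 70%: B = 1.7/1.3 = 1.308 and 2.4/1.6 = 1.5, so 7.5 and 12.2 points.

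**5. Can exact matching carry a longer list?** Gender, DM, HTN and intubation already form 2⁴ = 16 cells. Two centre levels and, for illustration, three calendar months give 16 × 2 × 3 = 96 cells for 115 recipients, about 1.2 each, before age, severity or co-treatment. With four controls wanted per recipient, the present rule would not survive the extension.

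**The case against.** Several points on the other side stand.
- Intubation is itself a severity marker, and eligibility already restricts recipients to serious disease. The gap is severity beyond intubation.
- APACHE, SOFA and inotropes appear only under Response Assessment, which follows infusion. No baseline value, and no value for controls, is stated. Used as listed, they could be affected by treatment.
- Centre and date are implied, not listed.
- An article may condense the time point for intubation, and a fuller document may name the regression covariates. The Discussion also discloses the lack of randomisation and the differences between centres.
- A score with many terms is likely to overfit at 40 versus 40.

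A reader might infer that all control of confounding rests on five variables. It does not: the logistic and Cox models adjust further, although that adjustment cannot be credited in detail. A reader might also call this confounding by indication. The controls are defined by refusal and lack of supply, not by a clinician's judgement of prognosis, so selection by consent, site and period describes it better. Nor does the document show that controls were sicker, came from earlier dates or came from lower-level centres.

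These points narrow the concern but do not remove it. The five-variable list is a stated choice made in two places, not a detail left open.

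**Conclusion.** The concern holds in limited form. The score omits baseline severity beyond intubation, illness duration and prior co-treatment, which the protocol records in some form, and centre level and calendar period, which it implies. For ICU stay, and for the bivariate, Kaplan-Meier and log-rank comparisons, no further adjustment is described. For 30-day mortality, the regressions may reduce the bias by an amount that cannot be judged from the text.

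Size and direction cannot be derived from the document. Under the stated assumptions, the spurious difference in unadjusted mortality is about 1.5 to 8 points if controls are sicker and about 1.6 to 12 points the other way if recipients are. The upper ends need a 40-point imbalance that persists after matching. Against a planned 11.6 points, even the middle of these ranges would matter. The claim that the plan is biased in favour of CP goes further than the text allows.

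**What to change.** Amend Study Population and Statistical Analysis together.

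1. **Index day.** Define one for controls, for example the same number of days since ICU admission or eligibility as the matched recipient's infusion.
2. **Score.** Add, using values on or before that day: SOFA or APACHE; oxygen or ventilation level including intubation; inotrope use; days since symptom onset; prior steroid, tocilizumab and antiviral use; centre level; calendar period.
3. **Matching rule.** Replace exact matching on all predictors with exact matching on index-day intubation, and at most one or two further key factors, plus caliper matching on the score. Aim for standardised mean differences below 0.1.
4. **Outcome models.** Adjust for any remaining imbalance, and include a model for ICU length of stay.
5. **Interim.** Use a reduced, severity-focused score at 40 versus 40.
6. **Optional.** Add a sensitivity analysis restricted to controls for whom plasma was unavailable, adjusted for centre level and period.

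The cost is revised analysis wording and the entry of index-day scores for controls. Some recipients may end up with fewer than four matches, which would cost some precision.
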